#### **2.1.5.Places of inclusion of children**

A total of 14 UNTAs will be selected for this study due to 7 UNTAs per health zone. The UNTA selection criteria are as follows:

- Have a good attendance: the selection will start from the most frequented UNTAs to the less frequented;
- Be geographically accessible;
- Be covered by a telephone network.

The table in appendix 6 shows the elements of the UNTA typology including the average monthly attendance, the percentage of malnourished children admitted per month, the number of population served by the health area, the number of trained staff in post, the number of days disruption of inputs (average per month), the days of PCIMA activity.

Chart 7 : Health areas selected for the study

| Bonzola health zone | Nzaba health zone |
|---------------------|-------------------|
| 1 Mudiba            | 8 Of the market   |
| 2 Solola            | 9 Tudikolela      |
| 3 Tubondo 2         | 10 PMKO           |
| 4 Dubai             | 11 Lutulu         |
| 5 Kashala Bonzola   | 12 Airport        |
| 6 Nyongolo          | 13 Tarmac 2       |
| 7 Lubilanji         | 14 Tatu muya      |

### 2.1.6. Sample size

The size needed for this work will be calculated according to the following formula:

$$N = (Z_{1-\alpha} + Z_{1-\beta})^2 \times 2 \sigma^2 / (\Delta - \delta)^2$$

Or :

$\alpha$  represents the error of the first kind;  $\beta$ , error of the second kind;  $\Delta$ , the Non-inferiority Margin;  $\sigma^2$ , Estimation of the variance and  $\delta$ , Possible difference in expected efficacy between the standard dose and the reduced dose. As  $\alpha = 0.05$  then  $Z_{1-\alpha} = 1.64$  and  $Z_{1-\beta} = 0.84$  (38) (39) (40).

In this study the mean rate (SD) of weight gain for each participant is 5 g / kg / day (2.6) and the expected difference between the two groups (control and intervention groups) will be 0 g / kg / day with a non-inferiority of 0.5 g / kg / day. The minimum acceptable average rate of weight gain in any group will be 4.5 g / kg / day. Assuming a power of 80% and a significance level of 5%, 335 children are needed in each group to verify that the maximum true difference between the intervention groups is not more than 0.5 g / kg / day . Taking into account a dropout rate of 20%, the total sample size was rounded to 1,000 children.

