## **Research hypotheses**

### **Main hypothesis**

Children receiving the reduced dose will have the same weight gain from admission to discharge as children receiving the standard dose of RUTF with a non-inferiority margin of 0.5g / kg / day.

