### **2.3.3. Statistical analyzes**

For the quantitative part of the study, the data will be summarized in Mean and Standard Deviation if they are normally distributed (normality test) for continuous variables and in absolute and relative frequencies for categorical variables.

The t-test and the chi-square test will be used respectively to compare the means and the proportions of the socio-demographic characteristics at admission for the quantitative and qualitative variables.

Linear regression analyzes will be used to determine the significant differences between the 2 groups of children for the quantitative variables.

Binary logistic regression analyzes will be used to determine the significant differences between the 2 groups of children for the binomial qualitative variables (2 response modalities).

Multinomial logistic regression analyzes will be used to determine the significant differences between the 2 groups of children for the multinomial qualitative variables (3 or more modalities).

All analyzes will be done in an adjusted and unadjusted model and a difference is statistically significant when the P-value is less than 0.05.

The results will be analyzed using statistical software, in this case STATA, version 17.

The main analyzes will be done by intention to treat (ITT) and per protocol for the main result, in this case, the speed of weight gain. The other secondary results will be analyzed only by intention to treat (ITT).

For the DPM, a score will be assigned to the participant and the sum will constitute the total score for each participant per domain.

For focus group data, after transcription of the recordings into Word 2019, thematic analysis will be done using Excel tables (matrix) or Nvivo® software.

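### A 20% dropout on 335 per group gives 838 children, not 1,000; the loss or the power behind 1,000 should be restated

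*Protocol*

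**What the plan says.** Section 2.1.6 gives a non-inferiority formula for two means with Z(1−α) = 1.64 and Z(1−β) = 0.84, a mean weight gain of 5 g/kg/day with SD 2.6, and a true difference of zero: "the expected difference between the two groups (control and intervention groups) will be 0 g / kg / day". The main hypothesis sets the test "with a non-inferiority margin of 0.5g / kg / day". The result is stated as "Assuming a power of 80% and a significance level of 5%, 335 children are needed in each group", and the enrolment total follows in one sentence: "Taking into account a dropout rate of 20%, the total sample size was rounded to 1,000 children".

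The total is carried consistently through the protocol. The Executive summary (Participants) recruits 1,000 children, and Annex 5 (Study population) counts 500 per arm.

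On the level of testing, section 2.3.3 offers one general rule for all regression models: "a difference is statistically significant when the P-value is less than 0.05". It does not say whether the test is one-sided or two-sided, and it does not mention the non-inferiority comparison or a confidence interval.

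**The concern.** A reader who follows section 2.1.6 line by line can reproduce the first figure but not the second. Adding a 20% allowance to 670 does not come near 1,000, and the gap is too wide to be called rounding. Either 20% is not the loss that was really assumed, or 1,000 was fixed on other grounds. The text does not let the reader tell which.

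The enrolment target, and the power an ethics committee or a later reader will attribute to the trial, rest on this paragraph. As written, the stated 80% power and 20% dropout do not belong together with 1,000 children.

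A related point is that the one-sided level appears only through the value 1.64. The words never say one-sided, so the level on which the size depends is easy to lose when the analysis section refers only to P < 0.05.

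**Working it through.** **Inputs**

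- One-sided α = 0.05, from Z(1−α) = 1.64 (2.1.6)
- Power 80%, from Z(1−β) = 0.84 (2.1.6)
- SD σ = 2.6, expected difference δ = 0, margin Δ = 0.5 g/kg/day (2.1.6; Main hypothesis)
- Equal allocation (2.2.1; 500 per arm in Annex 5)
- Dropout 20% (2.1.6)

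**Step 1: reproduce the stated size per group**

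n = (Z(1−α) + Z(1−β))² × 2σ² / (Δ − δ)²

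With unrounded normal quantiles (1.645 and 0.842 to three decimals), this is 334.4, rounded up to **335**. With the protocol's rounded values, (1.64 + 0.84)² × 2 × 2.6² / 0.5² = 332.6, or 333. The protocol's 335 is therefore confirmed.

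**Step 2: apply the stated dropout**

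- Dividing by the retained fraction: 335/0.8 = 418.75, so 419 per group. In total, 670/0.8 = 837.5, so **838**.
- Multiplying by 1.2, the cruder shortcut: 670 × 1.2 = **804**.

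Neither rounds to 1,000. The excess over 838 is 1,000 − 838 = 162, and 162/838 = 19%.

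**Step 3: the loss that 1,000 implies**

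1 − 670/1,000 = 0.33. The step from 335 per group to 1,000 in total corresponds to about **33%** loss.

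**Step 4: the power that 1,000 delivers**

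Power = Φ(Δ / (σ√(2/n)) − z), where n is the number evaluable per arm.

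- n = 400 (20% lost): standard error 2.6 × √(2/400) = 0.1838 and 0.5/0.1838 = 2.72.
- n = 500 (all analysed): standard error 2.6 × √(2/500) = 0.1644 and 0.5/0.1644 = 3.04.

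| Evaluable per arm | One-sided 5% (z = 1.645; two-sided 90% interval) | One-sided 2.5% (z = 1.96; two-sided 95% interval) |
|---|---|---|
| 335 | 80.1% | 70.2% |
| 400 | 85.9% | 77.6% |
| 500 | 91.9% | 86.0% |

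**Step 5: the size if a two-sided 95% interval were intended**

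The formula in step 1 with z = 1.96 gives 424.5, so 425 per arm and 850 in total. After 20% loss this is 850/0.8 = 1,062.5, so 1,063. On that reading only, 1,000 is slightly short of 80% power.

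**The case against.** The strongest reply is that the error is harmless. The core figure of 335 is right, 1,000 exceeds what the stated inputs require, the total is used consistently, and the promised 80% is met and passed at the planned level. All of that stands. It limits the point to a derivation that does not produce its own total; it does not make 1,000 a rounding of 838.

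Two stronger readings are tempting, and the protocol supports neither.

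*That 1,000 is an error and 838 is the correct target.* Section 2.1.4 limits the per-protocol analysis of the primary outcome to children declared cured. That set loses deaths, non-responders and other non-cures as well as dropouts, so its loss may exceed 20%. Annex 4 (Context and rationale) says cure in outpatient care often exceeds 75%. Taking 75% purely as an illustration, 838 enrolled would leave about 314 per arm (419 × 0.75), below 335, with about 78% power at one-sided 5%. Enrolling 1,000 would leave 375 per arm (500 × 0.75) and about 84%. The protocol does not offer this as its reason, so the explanation is still missing, but it is a good argument against cutting the target.

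*That the trial has only 78% power because section 2.3.3 uses P < 0.05.* That rule is a general one for declaring differences. It does not say two-sided, and it is not tied to the non-inferiority conclusion. The size calculation itself uses one-sided 5%, and a statistical analysis plan, which was not available here, may fix the interval. The 78% also assumes 400 evaluable per arm. If all 500 enter the intention-to-treat analysis, even the two-sided 95% reading gives 86%.

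**Conclusion.** The point holds as a discrepancy in section 2.1.6. The stated inputs and 20% dropout lead to 838, while the protocol enrols 1,000, a figure that matches about 33% loss. The mismatch is 162 children and is in the safe direction. At the planned one-sided 5%, power is about 86% with 400 evaluable per arm and about 92% with all 500, assuming SD 2.6, no true difference and a margin of 0.5.

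It is not a finding that the trial is underpowered, nor that too many children are enrolled, nor that sections 2.1.6 and 2.3.3 contradict each other. The 78% applies only if a two-sided 95% interval is intended and 20% of children are not evaluable. The correction is worth making because the paragraph justifies the enrolment target and is cheap to put right.

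**What to change.** Keep 1,000 and rewrite the last sentences of section 2.1.6 in one of two ways, whichever is true:

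- **State the loss actually assumed.** For example: 335 evaluable children per group are needed (one-sided 5%, 80% power); allowing for about 33% not evaluable, 1,000 are enrolled. If the allowance is meant to cover the per-protocol set of cured children, say so.
- **Keep 20% and state the power.** For example: 335 per group would require 838 in total after 20% dropout; 1,000 will be enrolled, leaving 400 evaluable per arm and about 86% power at one-sided 5%. Add the reason for choosing 1,000.

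In either case, add to 2.1.6 and 2.3.3 that non-inferiority is judged at the one-sided 5% level, equivalent to a two-sided 90% interval, as used for the size. If a two-sided 95% interval is intended instead, state that power with 400 evaluable per arm is about 78%.

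The cost is one paragraph in 2.1.6 and a phrase in 2.3.3. Enrolment does not change, and neither does the analysis if the planned one-sided level is confirmed.

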### 2.1.7. Recruitment

Patients will be recruited from the UNTAs whether they come directly from the community, screened by the RECOs or whether they are referred from the HCs. Community intermediaries will ensure awareness in order to facilitate recruitment within the allotted time. We plan to enroll 2-3 children per day per UNTA. Which will take about 2 months for the recruitment.

On admission, anthropometric measurements including weight, height, MUAC and nutritional edema will be taken on all children. The gender and age of the children will also be entered upon admission.

On admission, for each child, in addition to anthropometric measurements:

- Psychomotor development will be assessed by a score;
- A socio-demographic questionnaire including a food insecurity score will be administered to the caregiver.

All participants will be recruited on the basis of informed consent of information given in the language of the caregiver, followed by a written and signed agreement. Confidentiality will be ensured for each individual who will be selected for the study via the anonymization of questionnaires and data protection.

## **2.2. Randomization**

### **2.2.1. Sequence generation**

Randomization by blocks of variable size will be used in this study in each of the 14 UNTAs. In order to ensure that the participants are evenly distributed, in each block there will be the same number of children from each group(41) (42).

### **2.2.2. Randomization concealment mechanisms**

Once the randomization lists are generated, they will be printed and kept in two copies, one at the ACF headquarters in Paris and the other at the ESP in Kinshasa. The randomization list for each UNTA will be sent by sealed envelope to the nurse in charge of the corresponding health area (IT). Researchers will not have access to the footage. Only ITs will have access to the randomization sequences of the corresponding UNTA.

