### **2.2.3. Implementation**

Randomization will be done using [www.randomization.com](http://www.randomization.com) by an independent person who will not participate in the implementation of the study. Study participants will be recruited from the 14 UNTAs (due to 7 per ZS) selected and upon admission each will receive a unique identifier corresponding to their group in the study. The IT will receive special training to enable it to know how to randomly assign the identifier to UNTA participants.

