### **2.2.4. Blinding (masking)**

The statistician who will do the randomization will send the results in closed envelopes which will only be opened by the ITs of each selected UNTA. Neither the nurses who will take the anthropometric measurements nor the researchers will know which group each child

participating in the study belongs to. Due to the differing amounts of total RUTF sachets distributed, parents may deduct the dose their children will receive and thus not be blinded.

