## **IT in the UNTA (nurses):**

- Participate in research protocol training
- Recruit trial participants according to the inclusion criteria;
- Collect informed consents and keep them locked up before transmitting them to the principal investigator;
- Conduct medical and nutritional consultations with anthropometric measurements;
- Divide the participants into the two groups;
- Distribute RUTF to participants according to their group (control or intervention);

- Report / call by phone to find out how to manage any particular case asking questions about the research protocol, keep a debriefing time at the end of the week to share with researchers the constraints encountered and find solutions together
- Inform of any absences and replacement

**Socio-anthropological investigators** (assistants and note taker):

- Identify, with help from community relays, focus group participants and in-depth interviews;
- Obtain informed consent from participants in focus groups and in-depth interviews;
- Lead in-depth interviews and focus groups;
- Ensure note-taking during in-depth interviews and focus groups;
- Ensure the recording of in-depth interviews and focus groups with the permission of the participants; transcribe each interview into French in an anonymized Word document with unique identifying number and date, and keep the confidential register of corresponding identifiers and identities up to date
- Transmit to investigators the recordings and transcriptions made and the identification register.

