## **f. Organization of the collection**

### ***At UNTA level***

On admission, if a patient meets the study inclusion criteria, the receiving provider explains how the study is going and requests informed consent to include them in the study. If consent is obtained, the nurse assigns an ID to the child that matches the randomization ID. The randomization group is not mentioned. Information on socio-demographic characteristics is collected by IT.

The provider responsible for medically examining the child and taking the anthropometric measurements examines and provides information on the measurements. Anthropometric measurements will be taken according to the PCIMA protocol once a week when the child visits the center until the cured discharge or up to 12 weeks maximum.

- PB will be measured using a PB tape on the left arm halfway between the acromion and the olecranon;
- The weight using a SECA scale depending on whether or not the child can stand up;
- The height will be measured using a wooden measuring board in the supine or upright position depending on whether the child is <24 months or ≥24 months (or ≥ 87 cm) respectively;
- Edemas will be assessed according to their importance (0; + if limited to the feet; and ++ if limited to the legs).

The medical treatment is given to the child according to what is defined in the PCIMA protocol.

Finally, the child receives the amount of RUTF planned for the week as well as health education. It is the same provider in charge of the admission who will ensure the distribution of RUTF and will know who receives the reduced dose according to the IDs of the children. This provider will not follow up on children to keep blind. Each participant receives the quantity of RUTF described in Table 1 (presented above).

All the information on the identifier, the socio-demographic characteristics and the anthropometric measurements are noted in the individual follow-up sheet of the corresponding participant.

**Assessment of psychomotor development:** Depending on the sampling interval, the evaluation of psychomotor development will be carried out on 40% of the sample size, by means of the ASQ 3 score and will include two parts: the execution of the tasks by the child and the filling

of the questionnaire by the guides. For each child, the performance will only last between 10 to 15 minutes. The results of the assessment of psychomotor development are listed in the corresponding item.

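### The nurses who recruit hold each site's randomisation list, so allocation is not concealed; the role list also leaves blinding of the weight measurer unsecured

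*Protocol*

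**What the plan says.** **Who holds the sequence.** Section 2.2.2, the section on concealment, says: "The randomization list for each UNTA will be sent by sealed envelope to the nurse in charge of the corresponding health area (IT"). It adds: "Only ITs will have access to the randomization sequences of the corresponding UNTA". Copies stay at the sponsor's Paris headquarters and at the School of Public Health in Kinshasa. Section 2.2.4 says that the ITs alone open what the randomising statistician sends.

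**Who recruits and allocates.** Under the heading for the IT in the UNTA, the role list in 2.3.1 includes "Recruit trial participants according to the inclusion criteria", the collection of consent, "Divide the participants into the two groups" and the distribution of RUTF by group. Section 2.3.1 f (At UNTA level) has the receiving provider ask for consent and the nurse assign the ID. The provider who handles admission then dispenses RUTF and knows the arm from the ID.

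**Who measures.** The same IT role list includes "Conduct medical and nutritional consultations with anthropometric measurements". Section 2.2.4 says: "Neither the nurses who will take the anthropometric measurements nor the researchers will know which group" each child is in. Section 2.3.1 f describes a provider responsible for examination and measurement, and says of the dispensing provider: "This provider will not follow up on children to keep blind".

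**The identifier.** Section 2.2.3 says that on admission "each will receive a unique identifier corresponding to their group in the study". Section 2.3.1 f has the ID and the anthropometric measurements recorded on the same individual follow-up sheet, and says that the group itself is not mentioned.

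**The concern.** There are two separate problems.

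**Concealment.** Randomisation protects the comparison only if the person deciding on entry cannot know the next assignment. Here the recruiter has the site's sequence. Variable block sizes (2.2.1) make the next allocation hard to guess, but they give no protection against someone who can read it. Entry also involves some judgement: oedema grade, the appetite test, the exact MUAC reading, and how consent is discussed. Selection at this stage would make the arms differ at baseline in ways the analysis cannot reliably undo.

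**Blinding of the weight measurer.** The primary outcome is discharge weight minus admission weight, divided by initial weight and by duration of treatment (Annex 8). Each parameter is read once per visit (2.3.1 a). The same weekly measurements decide when the discharge criteria are met. A measurer who knows the arm could therefore affect both the weight difference and the duration.

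**Working it through.** **Step 1. Set the sections side by side.**

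| Task | 2.3.1 role list | 2.2.2 / 2.2.4 | 2.3.1 f |
|---|---|---|---|
| Hold and open the sequence | not listed | IT | not stated |
| Recruit, take consent | IT | not stated | receiving provider |
| Assign the arm | IT | not stated | the nurse, through the ID |
| Dispense RUTF | IT | not stated | admission provider, who knows the arm |
| Measure weight | IT | nurses unaware of the group | a provider responsible for measurement; the dispenser stays out of follow-up |

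**Step 2. Concealment.** In the role list, recruitment, consent and assignment all belong to the ITs, who are the only site staff with the sequence. In 2.3.1 f, UNTA staff again take consent and assign. Assigning the ID after consent does not help if the list is already open. No section mentions one envelope per child, sequential opening, off-site release, or a rule on when an allocation may be seen. Concealment fails on either description.

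**Step 3. Blinding.** The measurement row is contradictory: the role list gives it to the ITs, while 2.2.4 and 2.3.1 f give it to someone without the allocation. Section 2.3.1 b plans two providers per UNTA, so a split is possible, but the role list does not make one. A separate measurer would still handle the sheet carrying the ID. The protocol does not say whether that ID can be read as an arm without the list.

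**Step 4. The plan's own figure.** Inputs from 2.1.6: SD 2.6, margin 0.5, expected difference 0, one-sided alpha 0.05, power 80%.

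n per arm = (z₁₋α + z₁₋β)² × 2σ² / Δ²

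- With the rounded z values: (1.64 + 0.84)² × 2 × 2.6² / 0.5² = 332.6.
- With unrounded z values: 335, as stated.

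Nothing in this point changes the sample size.

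**Step 5. Scale of the margin.** 0.5 / 2.6 = 0.19 SD. In weight, the margin is 0.5 × kg × days. With assumed weights and durations:

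- 5 kg, 28 days: 70 g
- 7 kg, 42 days: 147 g
- 10 kg, 84 days: 420 g

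**Step 6. Illustration with assumed bias.** With 335 per arm, SE = 2.6 × √(2/335) = 0.201. Suppose the true difference lies exactly at the margin and a bias b favours the reduced dose. The chance of wrongly declaring non-inferiority is Φ(b/SE − 1.645).

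| Assumed b (g/kg/day) | One-sided error |
|---|---|
| 0 | 5% |
| 0.1 | 12.6% |
| 0.2 | 25.8% |
| 0.3 | 44.0% |

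These values of b are not estimates. Bias in the other direction would make a false claim less likely and cost power.

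**The case against.** The strongest defence concerns blinding. A reader might infer from the role list that one nurse does everything and that the measurer is therefore unblinded. The documents do not support that. Section 2.3.1 f is the operational description: it separates measurement from dispensing, keeps the dispenser out of follow-up and leaves the group unmentioned. Section 2.2.4 agrees with it. The role list pools the tasks of UNTA nurses in the plural. This defence stands, and it reduces the blinding half to a contradiction that must be settled.

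Other tempting inferences also go too far:

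- **A single envelope per site.** Section 2.2.2 uses the singular and 2.2.4 the plural, so the number is unclear. This does not rescue concealment, because what is sent is described as the UNTA's list.
- **An ID that encodes the arm.** Any ID used for dispensing must map to an arm. The text fits a look-up as well as a code.
- **Free choice among siblings.** Section 2.1.2 admits only the first. Numeric thresholds and the tabulated appetite test narrow discretion further, though they do not remove it.
- **The margin in SD units as the size of the bias.** It only rescales the margin.

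None of this answers the concealment half. A sealed envelope protects the list until it is opened, and the person who opens it recruits.

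**Conclusion.** Allocation is not concealed in the plan as written, because staff who recruit, take consent and assign also have the site's sequence and nothing limits what they see to one child at a time. This holds under both the role list and 2.3.1 f, and it should be corrected before enrolment.

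Blinding of the weight measurer is not secured, because the role list conflicts with 2.2.4 and 2.3.1 f, and because the ID from which the dispenser knows the arm is on the measurement sheet. By itself this calls for reconciling the text; it is not evidence of an unblinded outcome.

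The size and direction of any resulting bias cannot be derived from the protocol. The error rates above rest wholly on assumed biases. They show only that a shift well inside the margin would matter.

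**What to change.** 1. **Sequence (2.2.2).** Keep the full lists only at the two central offices that already hold copies. Supply each UNTA with sequentially numbered, opaque, sealed envelopes, one per child.
2. **Opening rule (2.2.2, 2.2.3, 2.3.1 f).** Open envelopes strictly in order, and only after eligibility, consent and admission measurements are recorded. As 2.3.1 f is written, the ID matched to the randomisation is assigned before the measurements are described, so the order of steps needs rewording.
3. **Identifier (2.2.3).** State that the ID on the follow-up sheet does not reveal the arm to the measurer.
4. **Roles (2.3.1).** Rewrite the IT list to match 2.2.4 and 2.3.1 f. Of the two providers already planned per UNTA, one opens envelopes and dispenses, and the other takes all measurements without access to allocations.

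The envelope holder may still be the admitting provider, so concealment depends on the opening rule more than on the role split.

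**Cost.** About 1,000 envelopes to print and some rewording; no new post and no change in sample size. With two providers, one absence breaks the split. The role list already foresees absences and replacements, so a cover rule is needed.
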